### Research design

2.1

This research project stems from a request from social workers to systematically evaluate their practice, i.e. the SAP program. This request from the practitioners has fundamentally affected the research design of the project. The project goal is to build scientific knowledge that is relevant and useful for practice and to design an evaluation that is feasible in the context of everyday social service practice. Such partnership between the social workers and the researchers can generate evidence about the preventive efforts used by practices [14]. Moreover, not only the intervention should be culturally competent, but the evaluation needs to be as well [15]. Therefore, we have adopted a culturally informed approach to evaluation of the SAP program. Fig. 2 presents the overall model for the evaluation. The model is based on Johnston and Smith's [16] recommendations concerning how practice-based evidence is best developed. Although a randomized controlled trial (RCT) is considered to be the golden standard when evaluating the efficacy and effectiveness of interventions the validity of RCT, at least in the first attempts to evaluate a program involving ethnic/cultural minority groups, or marginalized groups in general, has been questioned [17]. We want to proceed with caution and have evidence that SAP is acceptable to social workers and parents, and effective in achieving the primary outcomes in a smaller group of participants, before delivering SAP to larger groups of parents and conducting an RCT. In the exploratory phase, where the evaluation process of SAP currently is, other designs, single-subject oriented designs in particular, have been recommended as a first choice [17]. The first phase of the evaluation of SAP was carried out during the preparatory year funded by the Public Health Agency of Sweden in 2019. During that phase, we identified the program theory and logical model behind SAP and evaluated its theoretical potential to achieve the desired outcomes. We concluded that the SAP program was a theoretically promising intervention. The current study protocol concerns the next evaluation phase 2021–2023, with a focus on "quantitative single case evaluation" and "interviews of participants and group leaders." The following stages, "randomized control trial" and "program dissemination" are not part of this protocol. Establishing high implementation quality is an important first step in evaluating interventions. If the implementation quality is low, an otherwise effective intervention will probably not have any beneficial effects. Based on previous research on implementation studies [18], we will monitor the implementation process closely through observations and leaders', mangers' and participants' “consumer satisfaction” reports.

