### Participants

2.2

The research project will be conducted in Sweden. The project has two target groups. The primary target group is parents living in deprived areas in different municipalities. The social services in the different municipalities will recruit parents to the intervention. The target parent group is parents of teenagers (children aged 12–18 years) who express worries that their teenage children will end up in risk environments, with substance abuse and crime. The parents will take part in the SAP program to increase their personal resources and foster parent-child communication to more adequately protect their children from negative developmental outcomes (i.e. substance abuse and delinquency). Parents of younger children and parents who are already participating in other parental support programs will be excluded. Because the availability of participants targeted by the SAP program is limited, the goal is an N of 30 parents that can be followed over time. In singles-subject oriented designs, a sample of *N* = 30 is considered feasible for analyses [19]. An oversampling of 30 individuals is calculated to adjust for non-consents and dropouts. Social workers who will deliver the SAP program in their municipalities constitute the second target group. All group leaders who delivered the SAP program (at least 2 in each municipality) and their managers will be asked to partake in interviews, fill in self-reports, and be observed by the program developers within the context of the current study.

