### Analysis

2.5

To answer the first three research questions (RQ1, RQ2, and RQ3), for which we will collect qualitative data through interviews with parents and SAP group leaders, we will use thematic analyses [27]. Thematic analysis includes descriptions of different patterns, or themes, provided in the data which generates a deeper understanding of the data material. To answer RQ3, we will also perform descriptive statistics of the group leader self-reports. To answer the fourth research question, we will use an interrupted time series design (ITSD, 17). ITSD is usually based on a series of within-individual measurements of the outcome before, during and after exposure to the intervention. The appearance of these series is compared to determine if SAP (thus the interruption) has any effect on the outcome. A difference between the pre-and post-tests indicates an effect of the intervention. Various exposed individuals' series are then studied to determine if identified patterns can be replicated. The advantage of ITSD is that data in this situation can be presented in a meaningful and informative way with the help of descriptive statistics and data visualization plotted on graphs and complemented with a celeration line [28]. With the help of these graphs, individual exposed (and non-exposed) time series can be presented and analyzed. If the celeration line differs between the different phases, changes in outcomes could be present. In addition, the conservative dual-criteria (CDC) method could be used with small data streams (<7). Using the binomial formula, the CDC method helps to judge whether the change in the variables was present relative to the baseline condition. Finally, Dallery et al.'s [29] recommendations will be followed to analyze visual representations of data.

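### Section 2.5 lets any pre/post difference indicate an effect and seeks replication among 30 parents, with no required number of parents and no chance count across them

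*Protocol article*

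**What the plan says.** The protocol article, section 2.5 (Analysis), answers RQ4 in steps.

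- Within a parent's series: "A difference between the pre-and post-tests indicates an effect of the intervention". No size of difference is given.
- For the graphs, the criterion is softer and also has no threshold: "If the celeration line differs between the different phases, changes in outcomes could be present".
- Across parents: "Various exposed individuals' series are then studied to determine if identified patterns can be replicated". No number or share of parents is attached.
- A chance benchmark appears once: "In addition, the conservative dual-criteria (CDC) method could be used with small data streams (<7"). It is linked to the binomial formula. No alpha, choice of phases to compare or rule for combining parents follows.

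Section 2.2 (Participants) sets the scale: "the goal is an N of 30 parents that can be followed over time". Section 2.3.2 (Effect) names three primary outcomes: parental self-efficacy, parent-child communication and parents' worries. The Abstract gives three measurements before, two during and two after the programme (3/2/2). Section 2.3.2 gives two, three and two (2/3/2).

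Section 2.1 (Research design) says what the result is for. The team wants evidence that the programme is acceptable and "effective in achieving the primary outcomes in a smaller group of participants, before delivering SAP to larger groups of parents", and then an RCT.

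**The concern.** Replication across cases is persuasive in single-case work when there are few cases and each change is unlikely to arise by chance. Neither condition is secured here. There are about 30 series, each with two or three scores before and two after, and the stated criterion is a difference of any size. Two short means of noisy questionnaire scores almost always differ, and without an effect they differ in the favourable direction about half the time. Finding the same pattern in further parents then says little unless the number found is compared with the number expected from noise.

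This needs no regression to the mean, no history effect and no shared time course. It arises with a stable population, independent parents and random error alone. Section 2.5 therefore fixes a rule that would tend to report a replicated effect where none exists, and that finding is part of the stated basis for moving to larger groups and an RCT.

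**Working it through.** **Plan's own figure.** N = 30 rests on a citation about feasibility, with no alpha, power or effect size, so there is no calculation to reproduce.

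**Inputs.** n = 30 parents (section 2.2); three primary outcomes (section 2.3.2); schedules 3/2/2 (Abstract) and 2/3/2 (section 2.3.2). Assumptions: no effect, symmetric error, independent parents. The article does not define replication, so it is taken as r = 2 parents or more, with r = 3 as a check.

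**Formula.** With q the chance that one parent shows the favourable pattern by noise, X is binomial(30, q) and

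P(X ≥ r) = 1 − Σ_{j<r} C(30, j) q^j (1 − q)^(30−j).

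**1. Stated pre/post rule.** Symmetric error gives q = 0.5.
- Expected number: 30 × 0.5 = 15.
- P(X ≥ 10) = 1 − P(X ≤ 9) = 1 − 0.021 = 0.979.
- P(X ≥ 2) = 1 − 31 × 0.5^30, which is practically 1.

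**2. CDC applied first.** If all k later points must lie beyond the baseline lines, the nominal chance per parent is q = 0.5^k. Results for one outcome:

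| Later points used | q | P(X ≥ 2) | P(X ≥ 3) |
|---|---|---|---|
| 2 post points (either schedule) | 0.25 | 0.998 | 0.989 |
| 4 (Abstract, 3/2/2) | 0.0625 | 0.567 | 0.288 |
| 5 (section 2.3.2, 2/3/2) | 0.03125 | 0.241 | 0.066 |

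Worked for the last row: 0.96875^30 = 0.386 and 30 × 0.03125 × 0.96875^29 = 0.373, so P(X ≥ 2) = 1 − 0.386 − 0.373 = 0.241.

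The q column is also the smallest p that CDC can return. It cannot reach 0.05 on two post points, nor on the Abstract's four later points. Only all five later points on the 2/3/2 schedule can.

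**3. Simulated CDC.** Normal series with no effect were generated, with baseline mean and trend lines raised by 0.25 SD and lag-1 autocorrelation from 0 to 0.6. P(X ≥ 2) for one outcome was:
- 0.95 to 0.97 for two pre against two post points;
- 0.93 to 0.97 for three pre against two post points;
- 0.41 to 0.76 for three pre against all four later points;
- 0.38 to 0.69 for two pre against all five later points.

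**4. Three outcomes.** If a replicated pattern on any one outcome may count, and the outcomes are taken as independent, the chance is 1 − (1 − P)^3:
- from 0.241: 1 − 0.759^3 = 0.56;
- from 0.567: 1 − 0.433^3 = 0.92.

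**5. What a chance level would require.** With q = 0.5 and 30 untied parents, P(X ≥ 20) = 0.049. Adding C(30, 19)/2^30 = 0.051 gives P(X ≥ 19) = 0.100. The smallest count at or below 0.05 is therefore 20.

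**The case against.** The strongest reply is that this is exploratory single-case work reported in a condensed article. A required count, an alpha and a multiplicity rule may stand in a fuller protocol or analysis plan that is not shown. The section also defers to published recommendations for visual analysis, whose content cannot be checked here. A false positive would lead to an RCT, and acceptability is weighed alongside effect. These points limit the consequence. They do not remove the defect, because the article does not merely omit detail: it states that a pre/post difference indicates an effect.

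Three stronger readings are tempting and should not be drawn.

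- *That the plan has no chance benchmark.* It names the CDC binomial method. What is missing is a benchmark across parents, an alpha, and a commitment to use the method.
- *That unchanged or worsening parents are ignored.* The text never says so. Asking whether patterns can be replicated leaves room for finding that they cannot. The plan simply gives no rule for how such parents enter the conclusion.
- *That noise nearly always produces replication, whatever screen is used.* This holds for the bare pre/post rule and for CDC on two post points. It does not hold for CDC over four or five later points on one outcome (0.57 and 0.24 nominally). With three parents required, the five-point figure falls to 0.066.

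The celeration-line sentence is also hedged, so the point rests on the pre/post sentence and not on that one.

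**Conclusion.** The point stands in this form: section 2.5 pairs an effect criterion of any size with a search for replication that has no required count and no chance comparison across parents. Followed literally, with no effect, about 15 of 30 parents would show a favourable difference and at least 10 would do so with probability 0.98.

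The optional CDC step reduces the problem by an amount that depends on choices the article leaves open. For one outcome and at least two parents, the nominal probability runs from 0.998 (two post points) through 0.57 (four later points) to 0.24 (five later points). It is higher if any of the three primary outcomes may carry the claim.

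These figures assume independent parents and symmetric error. The CDC figures also assume at least two parents as the meaning of replication, and the three-outcome figures assume independent outcomes. Parents who attend the same course may not be independent, and the calculation does not cover that. The correction should be made before the results are read as evidence of effect, but it does not call for a different design.

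**What to change.** Keep the individual graphs and the single-case analysis, and replace the replication sentence in section 2.5 with text to this effect:

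*For each primary outcome we report how many of all parents with a series improved, were unchanged and worsened. A pattern is called replicated only if the number improving exceeds chance in a one-sided sign test at 0.05, with ties excluded from the denominator. Alongside the single-case analysis we report a group-level estimate with 95% CI from a mixed model over all available measurements, with a phase term and a random intercept for parent. If any one of the three primary outcomes alone is to carry the effect claim, a Holm adjustment is applied.*

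With 30 untied parents the sign test requires at least 20 improving (p = 0.049). The cut-off must be recomputed for the number of untied parents actually available. If CDC is kept, state whether it will be used, on which phases and at what alpha, and reconcile the 3/2/2 and 2/3/2 schedules, since these decide whether it can reach 0.05 at all.

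The cost is a few sentences and a little more analysis of data already collected, with no extra participants or measurements. The downside is that some apparent individual successes will no longer count as evidence of effect.

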**Methods:**

SAP will be evaluated when implemented by social workers in three Swedish municipalities using a culturally-informed mixed design procedure. Parents will be recruited to the program by local social workers. Groups leaders will be interviewed, observed, and they will fill out self-reports to measure implementation quality, including fidelity and acceptability. A group of parents will be interviewed to better understand their perceived challenges and needs in their parenting in Sweden and their experience of participating in SAP. An interrupted time series design with three measurements before, two measurements during, and two measurements after the intervention has ended will be employed using self-reports of parental self-efficacy, parent-child communication, and parents' worries. Informed consent will be collected from all study participants.

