While the proposed research carries many advantages and has the potential to advance the field, it also has possible limitations and caveats. The proposed type of research comes with legion challenges that might threaten the validity of the research findings and even the feasibility of the project. One challenge involves reaching parents and recruiting them to the project. We believe that our close collaboration with local and culturally competent social workers will be important to tackle this challenge. Furthermore, the issue of ethnocentrism needs to be acknowledged [31]. One of the goals behind the SAP program is to help parents adjust to parenthood in Sweden and to obtain Swedish values in relation to parenthood (e.g., that open and bidirectional communication is a cornerstone of any good parent-teenager relationship). In trying to achieve this, it is important to be respectful in relation to what other cultural values parents may have. Another challenge relates to methodology and potential threats to validity. Among other things, history effects could affect the sustainability of the findings across time. Future studies are needed to handle this challenge. Further, the research design demands a lot from participants, including that they can read and that they have the motivation and possibility to fill out repeated measurements. It is possible that this will cause study attrition and exclude potential participants from taking part in the study. A final note has to do with the external validity of the findings. Future research is needed to test whether any detected effects are sustained across countries.

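### Replication is sought parent by parent although parents in one course very probably share start dates, so their agreement cannot rule out an outside event, and history is deferred to future studies

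*Protocol article*

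**What the plan says.** Section 2.5 (Analysis) gives the rule for RQ4: "A difference between the pre-and post-tests indicates an effect of the intervention". The series of different exposed individuals come next: these "series are then studied to determine if identified patterns can be replicated". The unit examined for replication is therefore the individual parent. Course, group leader and municipality do not appear in this part of the analysis.

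The same section says that "individual exposed (and non-exposed) time series can be presented and analyzed". It also names celeration lines compared between phases, and the conservative dual-criteria (CDC) method with the binomial formula as a possible aid.

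On delivery, the abstract states that "SAP will be evaluated when implemented by social workers in three Swedish municipalities". Section 2.2 (Participants) refers to "All group leaders who delivered the SAP program (at least 2 in each municipality" and adds their managers. Section 2.3.1 has leaders and managers interviewed for each course delivered, and ties measurement occasions to the start and end of the intervention. Table 1 refers to sessions. On sample size, section 2.2 says "the goal is an N of 30 parents that can be followed over time".

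On history, the Discussion says that "history effects could affect the sustainability of the findings across time. Future studies are needed to handle this challenge".

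**The concern.** In an interrupted series without a control, the main rival to a programme effect is something else that happened when the programme began. Replication guards against this only if the replicates start at different times. Parents who begin together face the same police operation, school-term change or news story in the same week. The worry scale in section 2.3.2 includes an item about the child being caught by the police, so such an event could move that outcome for a whole course.

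If agreement among those parents is read as repeated replication, one event can pass for many confirmations. Section 2.3.2 likens the causal properties of a well-executed interrupted time series to those of a randomised trial, and section 2.1 makes this phase the evidence of effectiveness sought before an RCT. Misplaced confidence here would carry into that decision.

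**Working it through.** **The plan's own figure.** The target of 30 parents rests on a citation about feasibility. No effect size, SD, error rate or power is given, so there is nothing to reproduce.

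**The passages side by side.**

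1. Section 2.5: a pre/post difference in one parent's series is an effect, and other parents' series are examined for replication.
2. Abstract, sections 2.2 and 2.3.1, Table 1: delivery is by group leaders, in courses made up of sessions, with measurement tied to the intervention's start and end.
3. From 2, parents in one course share leaders and sessions and very probably a start date. Their series then break at the same calendar time. This is an inference from group delivery and is not stated.
4. No staggered start, varied baseline length or comparison between courses is described.
5. Sections 2.2 and 2.3.2 describe no parents who do not receive SAP, so the non-exposed series have no described source.

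**Illustration.** Every input below except the numbers of measurements is assumed.

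- One course of 10 parents, no programme effect, independent normal errors within parents.
- b baseline points and 2 post points. The abstract gives b = 3 and section 2.3.2 gives b = 2. That conflict is a separate matter, so both are shown.
- A parent improves if the post mean exceeds the baseline mean.
- One outside event shifts every parent in the course by d within-parent SDs after the start.

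The probability that one parent improves is p = Φ(d / √(1/b + 1/2)). The divisor is √(1/2 + 1/2) = 1 for b = 2 and √(1/3 + 1/2) = 0.913 for b = 3. The number improving is then binomial(10, p).

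| Shared shift d | b | p | P(at least 8 of 10 improve) |
|---|---|---|---|
| 0 | 2 or 3 | 0.500 | (45 + 10 + 1)/1024 = 0.055 |
| 0.5 | 2 | 0.691 | 0.36 |
| 0.5 | 3 | 0.708 | 0.41 |
| 1.0 | 2 | 0.841 | 0.80 |
| 1.0 | 3 | 0.863 | 0.85 |

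A simulation gave each course its own random shift, in either direction, with SD 0.5 to 1 and no programme effect. The chance that at least 20 of 30 parents improve rises from about 0.05 to 0.14–0.22 with 3 courses of 10, and to 0.09–0.15 with 6 courses of 5. More courses with separate shocks reduce the problem, which is why the course is the informative unit for replication.

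The thresholds of 8 of 10 and 20 of 30 are illustrative. The plan sets none.

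**The case against.** The plan has no explicit counting rule. It says patterns will be studied for replication. It does not say that 30 parents are 30 independent confirmations, and it does not exclude comparison by course. How series are grouped could be set out in a fuller document. That is fair, but the rule as printed pairs a causal reading of each parent's difference with replication across individuals, and nothing in it guards against a shared start date.

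The CDC method and celeration lines do address chance and pre-existing trend. This stands: replication is not the plan's only safeguard. Neither tool separates SAP from an event that coincides with its start, so only the shared-calendar threat remains.

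The Discussion already raises history in the context of validity threats, and the phase is described as exploratory with an RCT to follow. This too stands, and it makes part of the remedy a matter of wording. But the consequence is described as one of sustainability and is handed to other studies, although it bears on whether this study's own changes are due to SAP.

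The mention of non-exposed series is loose and permissive, not a commitment to a comparison group. It needs a source or deletion, no more.

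A reader might infer two stronger points. One is that there are only three independent replications. That needs one course per municipality, which is not stated; the wording about each delivered course and a phase running 2021–2023 are compatible with several courses on different dates. The other is that standard errors will be too small by a calculable amount. The plan describes no pooled model or standard error, and gives no intraclass correlation or course size.

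**Conclusion.** The concern holds in a limited form. As written, the RQ4 analysis seeks replication across individual parents without regard to course. Agreement among parents who start together is not independent replication against a calendar explanation. History is described too narrowly for an uncontrolled interrupted series, and the non-exposed series are unsourced.

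The conclusion rests on one inference, that parents in a course share a start date. This is very probable under group delivery but is not stated. The size cannot be fixed, because the number, size and dates of courses are not given; the figures above show only that a moderate shared shift is enough to mislead. If courses already start at different times, much of the protection is available and only has to be used.

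**What to change.** In section 2.5:

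- Record calendar dates for every wave and every course start. Plot and summarise the series by course.
- Count replication across courses with different start dates. Report agreement within a course as supporting evidence only.
- Where course dates already differ, use baseline waves of courses not yet started as the non-exposed series, provided they overlap in calendar time with another course's intervention or follow-up. A course in another municipality helps only against events that reach both. If no such overlap exists, delete the reference to non-exposed series.
- If a pooled model is fitted, account for course.

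In the Discussion, in either case, name history as an internal-validity limitation of this study.

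The cost is fewer stated replications and a little more analysis work. No new participants or instruments are needed. Deliberate staggering of course starts would strengthen the design, but it would need coordination with the municipalities and possibly longer baselines; it is optional.
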